## 2. Methods

### 2.1. Aim

The aim of this randomized controlled trial is to directly compare the effects of two different exercise modalities, power cycling and quadriceps training combined with online guidance separately on KOA mitigation of pain in patients with KOA in a community, compared to the control group. We hypothesize that there will be a difference between these two rehabilitation strategies. Our secondary aim is to compare the effectiveness of two different exercise modalities on other outcomes, including quality of life, improvement of functional physical performance, adherence of participants.

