### 2.9. Sample size

The calculation is carried out according to the standard for the sample size of noninferiority trials and the unified standard for clinical trial reporting.^[38,56]^ Based on the degree of reduction in WOMAC pain scores was used as an index to assess the improvement in symptoms of KOA with each type of exercise. The literature was reviewed to obtain the means and standard deviations of changes in pain scores in the three groups of patients with KOA,^[42,57]^ The sample content estimate formula shows that, for a significance level of 0.05 and a yielding power of 90%,

$$\begin{array}{l} n=\varphi^{2}\left[\sum_{i=1}^{k}S_{i}^{2}/k\;\right]/\left[\sum_{i=1}^{k}{\left({\bar{X}}_{i}-\bar{X}\right)}^{2}/\left(k-1\right)\;\right]\; \end{array}$$

the sample size consists of 20 participants in each group. With a 20% dropout rate taken into account, each group needs 24 enrolled participants.

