### 2.11. Randomization and blinding

After baseline measurement, participants will be randomized 1:1:1 to the power cycling group, quadriceps group or control group using simple randomization. A table of random numbers will be produced using the computer soft SPSS (V21.0). Write the random number assigned to each group on a piece of paper and place it in an opaque envelope. Based on the order in which participants were enrolled, an independent biostatistician will randomly distribute envelopes to participants. Physicians and physiotherapists will receive standardized training prior to the start of the study and will be randomly assigned to three groups during the trial. Participants won’t be blinded because of the nature of the intervention; instead, they will only know their own grouping. Evaluators, statisticians, and data managers will be blinded during the trial.

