### 2.14. Statistical analysis

Analyses will use an intention-to-treat analysis strategy. We will use one-way ANOVA to determine baseline comparability between groups for quantitative variable data. Baseline comparability between groups of categorical variable data will be determined using the chi-square test or other suitable nonparametric tests. Quantitative data will be expressed as the mean; if it follows normal distribution and homogeneity of variance, otherwise median is given. In statistical inference, if the data obeyed a normal distribution, and homogeneity of variance and satisfied spherical symmetry, repeated measures data analysis of variance was used; if the data did not obey a normal distribution or the variance was unequal, the Kruskal–Wallis H rank sum test was used for data analysis. SPSS (V21.0) will be used for data analyses. We considered *P* ≤ .05 to be statistically significant.

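### Section 2.14 names only three-group tests, so a significant P value alone would not support the hypothesised difference between power cycling and quadriceps training

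*Protocol article*

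**What the plan says.** The aim (2.1) compares the two exercise programmes, each with online guidance, and brings in the third arm ("compared to the control group"). It then states one hypothesis: "We hypothesize that there will be a difference between these two rehabilitation strategies". Under 2.11, "participants will be randomized 1:1:1 to the power cycling group, quadriceps group or control group".

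For inference, 2.14 gives two branches. If normality and the other assumptions hold ("homogeneity of variance and satisfied spherical symmetry, repeated measures data analysis of variance was used"), the analysis is repeated-measures ANOVA. Otherwise, "if the data did not obey a normal distribution or the variance was unequal, the Kruskal–Wallis H rank sum test was used for data analysis". The criterion is "We considered *P* ≤ .05 to be statistically significant". The section names no pairwise contrast, no follow-up test and no rule for several comparisons.

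Section 2.9 sizes the trial "for a significance level of 0.05 and a yielding power of 90" per cent, using a formula that compares the spread of k group means with the average within-group variance. That is the omnibus one-way ANOVA formula. It gives 20 per group, raised to 24 for dropout. The means and SDs put into it are said to come from the literature but are not printed.

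**The concern.** The stated hypothesis concerns two arms. Its null is that cycling equals quadriceps training, whatever happens in the control arm. With three arms, the Kruskal–Wallis test and the group and group-by-time tests of the repeated-measures ANOVA have a different null: cycling, quadriceps and control are all equal. That null is false as soon as any one arm differs.

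Suppose the two exercises work equally well and both do better than education plus medication. The tests named in 2.14 are then expected to be significant, although the stated hypothesis is false. A significant result also does not say which arm differs, so on its own it answers neither the cycling-versus-quadriceps question nor either comparison with control. At stake is whether the P value produced by 2.14 can carry the conclusion that 2.1 sets out to reach. This would remain even if the sample-size section were corrected.

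**Working it through.** **Inputs from the article.** k = 3 arms, 1:1:1 (2.11); α = 0.05 (2.9, 2.14); power 90% and 20 per group before dropout (2.9); assessments at baseline and weeks 4, 8 and 12 (2.8).

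**Inputs not given, so assumed.** Group means, SDs, within-patient correlation, the pattern of the effect over time, and the measure to which Kruskal–Wallis is applied. Effects are in SD units of the 12-week change score, with a common SD. Kruskal–Wallis is applied to change.

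**Step 1: the plan's own figure.** The formula in 2.9 is n = φ²·(mean S²) / [Σ(X̄ᵢ − X̄)²/(k − 1)]. Without the means and SDs, n = 20 cannot be rebuilt forward, so it is solved backward. For one-way ANOVA with 3 − 1 = 2 and 60 − 3 = 57 degrees of freedom, 90% power at α = 0.05 needs noncentrality λ = 13.35. Then φ = √(λ/(k − 1)) = √(13.35/2) = 2.58, and Cohen's f = √(λ/60) = 0.47.

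**Step 2: express that effect with the two exercises equal.** Let the means be (0, d, d) for control, cycling and quadriceps. The overall mean is 2d/3, and the sum of squares is (4/9 + 1/9 + 1/9)d² = (2/3)d². So λ = 20 × (2/3)d² = 13.33d². Setting this to 13.35 gives d = 1.00 SD. An effect of 1.0 SD is thus what the stated power implies, but only if the whole effect is exercise versus control. The article does not state that pattern.

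**Step 3: rejection rates of one-way ANOVA when cycling = quadriceps, n = 20 per arm (noncentral F).**

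| d (SD of change) | λ = 13.33d² | Omnibus rejects |
|---|---|---|
| 0 | 0 | 5% |
| 0.25 | 0.83 | 11% |
| 0.5 | 3.33 | 34% |
| 0.8 | 8.53 | 72% |
| 1.0 | 13.33 | 90% |

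In simulation, a direct cycling-versus-quadriceps t-test stays at about 5% for every d, because that null is true.

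**Step 4: other omnibus tests at d = 1.0, n = 20 (simulation).**
- Kruskal–Wallis: 88% with normal data, 84% uniform, 96% exponential.
- Group-by-time F over four visits, compound symmetry: 82–83% if the effect grows linearly to week 12, 93% if it is present from week 4.
- Main effect of group in the repeated-measures ANOVA: 27% to 99%, depending on within-patient correlation (0.3 to 0.7) and onset.

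The first two therefore span roughly 82–96%. The main effect is far less stable, and 2.14 does not say which ANOVA effect is to be used. If all 24 per arm are analysed, ANOVA rises to 95% and Kruskal–Wallis to 93%.

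**Step 5: does an omnibus gate followed by pairwise tests protect the claim?** With three groups, either all three are equal, and the gate limits error to 5%, or at most one pair is equal, and the single test of that pair limits it to 5%. Family-wise error therefore holds for one set of three comparisons. Repeated at weeks 4, 8 and 12, it becomes 3 × 3 = 9 tests and the argument no longer covers the whole set.

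**Step 6: cost in power.** A two-sample comparison of cycling and quadriceps training at 20 per arm has about 34% power for a 0.5-SD difference, before any loss to a gate or to Holm.

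**The case against.** The strongest reply is that this is an omission in a condensed article. The full protocol or an SAP may name the contrasts, and a repeated-measures ANOVA model can carry a cycling-versus-quadriceps contrast. The control arm is part of the aim, so a three-arm test is a natural first step and can serve as a valid gate. All of this stands.

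It also limits what may be inferred. A reader might conclude that the planned analysis cannot test the hypothesis at all. That is true only of the omnibus P value taken alone. A reader might assume that the investigators will treat that P value as deciding the hypothesis, but the article never says so. A reader might quote the 82–96% range as a property of the tests. It holds only under the assumed 1.0-SD advantage over control, equal exercises and 20 analysed per arm; with no advantage the rate is 5%. Finally, the introduction does not show that both exercises are already expected to beat this control. It reports that both relieve pain, without naming a comparator or an effect size.

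What the reply does not remove is the mismatch in what is stated. The article chose to print its tests, its fallback and its threshold, and all of them address the three-group question, as does the sample-size formula. The Kruskal–Wallis branch supplies no contrast unless pairwise tests are added.

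**Conclusion.** The point holds in limited form. The hypothesis in 2.1 is a two-arm contrast, the tests in 2.14 have a null that includes control, and nothing in the article links the two. A significant omnibus P alone would not support a difference between the exercises.

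How often this could mislead depends on inputs the article does not give. With equal exercises and 20 per arm, the one-way ANOVA rate runs from the nominal 5% when exercise has no advantage over control, through about one trial in three at 0.5 SD, to about nine in ten at 1.0 SD. These are rates at which the omnibus test is significant. They become false-positive rates for the stated hypothesis only if the omnibus result is read as evidence for it. The plan should rule that reading out.

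**What to change.** In 2.14, base the conclusion on named contrasts of WOMAC pain at one pre-specified time point (for example week 12) or one pre-specified summary over visits:

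1. cycling minus quadriceps, for the stated hypothesis;
2. cycling minus control;
3. quadriceps minus control.

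Give each a 95% CI. Control the three together, either by the omnibus test at .05 followed by pairwise tests at .05 (valid for three groups at that single time point or summary) or by Holm. If the Kruskal–Wallis branch is used, add the matching pairwise rank tests. State that an omnibus P alone will not be read as a difference between the two exercises.

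The cost is a few sentences and three contrasts, with no extra patients or data. The downside is that the cycling-versus-quadriceps claim becomes harder to reach, given the power shown in Step 6. That limit is better stated in the plan than left behind a significant omnibus result.

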### 2.8. Outcome measures

Outcomes for the trial will be chosen based on Osteoarthritis Research Society International recommendations.^[43]^ Table 1 summarizes the primary and secondary outcome measures. Outcomes will be measured at baseline (T_0_) and at 4 (T_4_), 8 (T_8_) and 12 (T_12_) weeks after the allocation (Table 2).

**Table 1 T1:** Outcomes of this study.

Measurements	Metric of measurement	Method of measurement	Time point of primary interest
Primary outcomes			
Self-reported pain	0–20 (higher scores indicate more serious pain)	Western Ontario and McMaster Universities osteoarthritis index (WOMAC) – pain subscale	baseline, and 4, 8, and 12 wk after allocation
Secondary outcomes			
Self-reported pain	0–10 (higher scores indicate more serious pain)	Numerical pain rating scale (NRS)	baseline, and 4, 8, and 12 wk after allocation
Quality of life	Standardized scores for every section (higher scores indicate more better social participation)	The MOS item short from health survey (SF-36)	
Self-reported function and stiffness	0–76 (higher scores indicate more serious dysfunction)	WOMAC – physical function and stiffness subscale	
Functional performance	Seconds (shorter time indicates better function)	Timed up and go test	
Adherence	0–100% (Higher ratios indicate better adherence)	The ratio of the number of completed HXCR sessions to the total number of sessions	12 wk after allocation

HXCR = Huaxi Cloud Rehabilitation, NRS = numerical pain rating scale, SF-36 = The MOS item short from health survey, WOMAC = Western Ontario and McMaster Universities Osteoarthritis index.

**Table 2 T2:** The participant timeline.

Time point	Study period				
	Enrolment	Allocation	Post-allocation		
	−T_1_	0	T_4_	T_8_	T_12_
Enrolment					
Eligibility screening	×				
Informed consent	×				
Allocation		×			
Interventions					
Education					
Medication					
Exercise					
Assessment					
Sociodemographic data	×				
Personal and medical history	×				
IPAQ Short	×				
Primary outcome			×	×	×
Secondary outcomes			×	×	×

IPAQ Short = International Physical Activity Questionnaire.

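### Unequal variance should not be a trigger for Kruskal–Wallis: the test does not remedy unequal spread and drops the repeated visits from the primary analysis

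*Protocol article*

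**What the plan says.** Section 2.14 gives a two-branch rule for inference. If the data are normal, have homogeneous variances and "satisfied spherical symmetry, repeated measures data analysis of variance was used". If they are not normal, "or the variance was unequal, the Kruskal–Wallis H rank sum test was used for data analysis". The two reasons for leaving the first branch are joined by 'or', so unequal variance is sufficient by itself. No option that allows for unequal variances is named.

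The primary outcome is WOMAC pain, scored 0 to 20 (section 2.8.1). Section 2.8 begins "Outcomes will be measured at baseline" and goes on to weeks 4, 8 and 12. The sample size in section 2.9 rests on the fall in pain: "Based on the degree of reduction in WOMAC pain scores was used as an index".

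**The concern.** The rule is stated in the text, so this is not a matter of detail left to an analysis plan. An analysis plan would have to contradict section 2.14 to repair it. Three things are wrong with it.

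- **Wrong remedy.** The null hypothesis of Kruskal–Wallis is that all arms have the same distribution. A rejection reads as a difference in pain level only if the arms share shape and spread. The rule sends data to the test because spread differs.
- **Lost structure.** Kruskal–Wallis takes one independent value per participant. It has no time factor and no group-by-time term, so it is not a counterpart of the repeated-measures analysis that it replaces.
- **Data-dependent hypothesis.** The first branch concerns mean pain over time; the second concerns equality of distributions. Preliminary checks on the outcome data decide which one is tested.

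Unequal spread is plausible in an exercise trial, where some participants respond or adhere and others do not. On a bounded score it tends to come with skew. A significant result from the fallback could then be reported as a pain effect although mean pain is the same in all arms.

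**Working it through.** **Inputs from the article.** Three arms; "the sample size consists of 20 participants in each group"; "With a 20% dropout rate taken into account, each group needs 24 enrolled participants". The step from 20 to 24 is reproduced by 20 × 1.2 = 24. (Division by 0.8 would give 25; that does not affect this point.) The 20 itself cannot be reproduced, because section 2.9 prints no means or SDs. The plan gives no error rate for the fallback, so there is none to reproduce.

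**Assumptions.** All means, SDs and distribution shapes below are assumed. The tests are run at P ≤ .05.

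**Formulas.** Kruskal–Wallis: H = [12/(N(N+1))] Σ R_i²/n_i − 3(N+1), divided by the tie correction 1 − Σ(t³−t)/(N³−N), and referred to chi-square with 2 degrees of freedom. The comparator is Welch's ANOVA.

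**1. Equal spread.** Kruskal–Wallis rejects in 4.8% to 5.1% of simulated trials with normal data. The test is sound when its condition holds.

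**2. Symmetric data, same centre, unequal SDs** (ratios 1:1:2, 2:3:4, 1:2:3, 1:1:3).
- 20 or 24 per arm: Kruskal–Wallis 5.3% to 6.6%.
- Section 2.11 uses simple randomization, so arm sizes can drift. Kruskal–Wallis rejects in 6.9% to 9.0% if the smallest arm has the largest SD (30/24/18 or 32/24/16), and in 3.1% to 4.7% if the largest arm has it (18/24/30 or 18/18/36). Averaged over simple randomization of 72 it rejects in 5.6% to 6.2%.
- Welch with normal data: 4.8% to 5.2% throughout. Plain one-way ANOVA: about 5.5% to 7.4% with equal arms and up to 15% at 32/24/16, so a return to plain ANOVA is no answer.

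**3. Bounded, skewed 0–20 scores with equal means.** Scores are beta-binomial with p = mean/20 and intra-class parameter ρ = [SD²/(20p(1−p)) − 1]/19. At mean 4, 20 × 0.2 × 0.8 = 3.2. SD 2.2 gives 4.84/3.2 = 1.5125 and ρ = 0.5125/19 = 0.027. SD 4.4 gives 19.36/3.2 = 6.05 and ρ = 5.05/19 = 0.266. Kruskal–Wallis rejection in per cent, over 20 and 24 per arm (20,000 simulated trials per setting):

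| SDs | mean 4 | mean 5 | mean 6 | mean 8 |
|---|---|---|---|---|
| 2.2/2.2/2.2 | 5 | 5 | 5 | 5 |
| 2.2/2.2/3.3 | 7–8 | 6 | 6 | 5 |
| 2.2/3.3/4.4 | 14–15 | 9–10 | 7–8 | 6 |
| 2.2/2.2/4.4 | 16–19 | 11–12 | 8–9 | 6 |

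Welch's test stays between about 4% and 7% in all these settings.

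**4. What differs in the worst cell.** At mean 4 the SD 2.2 distribution has median 4 and 3% of scores at zero. The SD 4.4 distribution has median 2 and 27% at zero. The medians are therefore 4/4/2 although the means are equal.

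**5. Another skewed shape (gamma).** With equal means and unequal SDs, Kruskal–Wallis rejects in 7.3% to 18.3%. With equal medians it rejects in 5.2% to 8.1%.

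**The case against.** The strongest objection is that the large figures are false positives only against a null hypothesis of equal means. In the worst cell the medians differ, so typical pain does differ between arms. Section 2.14 itself makes the median the summary when the assumptions fail. If treatment has no effect of any kind, randomised arms share one distribution and Kruskal–Wallis keeps its level. All of this stands, and it limits the size of the harm. It does not make Kruskal–Wallis a remedy for unequal variance, and it does not restore the visits.

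Three stronger readings are tempting, and the documents do not support them.

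- A reader might infer that a difference in spread alone produces many false pain effects. Where spread is the only difference (symmetric data, equal arms), rejection is 5.3% to 6.6%. The higher rates need skew as well.
- A reader might infer that the fallback falls well short of the planned power. That requires raw week-12 scores, and section 2.14 does not say that they are used. On change scores Kruskal–Wallis keeps about 88% power at an effect for which one-way ANOVA has 90%. A loss on raw week-12 scores would come from ignoring baseline, and plain ANOVA would share it.
- A reader might put a figure on how often the switch would occur. The article names no preliminary test, no visit and no arm-wise checking, so any such figure is guesswork.

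Which visit or summary the fallback would use may properly be left to the full protocol or analysis plan, and the point does not rest on that.

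**Conclusion.** The point holds as a fault in a stated rule. Unequal variance is made a sufficient reason to use a test whose interpretation needs equal spread and which cannot carry the group-by-time comparison. This part rests on the text and on the properties of the test, and it is certain.

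The numerical consequence is possible and usually modest. With equal mean pain, rejection is about 5–7% for symmetric scores and equal arms and 5–8% at SDs 2.2/2.2/3.3. It rises to 16–19% only in the corner of doubled SD and mean pain 4 out of 20, where the medians also differ. Every one of these figures depends on assumed means, SDs and shapes. The matter concerns the primary outcome of a 72-person trial and should be corrected.

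**What to change.** In section 2.14, delete unequal variance as a trigger for Kruskal–Wallis. Name one primary analysis of WOMAC pain that is used whatever the preliminary checks show: a repeated-measures mixed model of the week 4, 8 and 12 scores with arm, visit, arm-by-visit and baseline WOMAC pain. Use unstructured within-person covariance, with either arm-specific variances or small-sample-corrected robust standard errors. For outcomes measured once, use Welch's test. Keep Kruskal–Wallis only as a labelled sensitivity analysis.

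Other variance-robust longitudinal models would also serve. What matters is that one is fixed in advance and that it adjusts for baseline. The cost is a few sentences, with no new data or participants. The small downside is the loss of a few degrees of freedom for the extra variance parameters.

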## 3. Discussion

KOA is a chronic disease, and its rehabilitation is also a long-term process. Tele-rehabilitation allows patients to carry out rehabilitation training in a community environment, reducing the number of patient’s visits to the doctor, saving patients’ time and money, and reducing the burden on the medical system. If effective, this study will provide important data for current tele-rehabilitation practice for KOA in community settings. The obtained data are expected to inform the development of future large-scale research trials.

Different from the previous study, the innovation of this study is the first use of IoT technology for tele-rehabilitation in KOA. Second, the multichannel recruitment of participants, especially the online publication of recruitment information, the online clinic and the online collection of basic information of participants, as well as the subsequent whole rehabilitation process (including rehabilitation assessment, rehabilitation treatment and communication with the participants), are all done online, giving full play to the advantages of the Internet and the remote nature, breaking the time and geographical restrictions and bringing the distance between doctors, therapists and patients closer.

However, some challenges also exist in the proposed study. An important challenge in this study is for participants to learn how to use IoT-based applications smoothly, although we will go into detail on first use. Second, one of the issues that need attention in tele-rehabilitation is the compliance of participants, which will reduce the compliance of the participants due to various reasons such as pain and lack of motivation of the participants. In order to increase the enthusiasm of the participants to exercise, we will remind the participants to exercise 3 times a week through a WeChat applet, send rehabilitation education materials to the participants every week, and conduct a WeChat video with the participants.
